## Abstract

**Background:**

A considerable number of people with a mental illness are parents caring for dependent children. For those with a mental illness, parenting can provide a sense of competence, belonging, identity and hope and hence is well aligned to the concept of personal recovery. However, little research has focused on the recovery journey of those who are parents and have a mental illness. This randomised controlled trial aims to (i) evaluate the effectiveness of an intervention model of recovery for parents (Let’s Talk about Children) in three different mental health service sectors and (ii) examine the economic value of a larger roll out (longer term) of the parent recovery model.

**Methods:**

A two arm parallel randomised controlled trial will be used with participants, who are being treated for their mental illness in adult mental health, non-government community mental health or family welfare services. The study will involve 192 parents, who are considered by their treating practitioner to be sufficiently well to provide informed consent and participate in an intervention (Let’s Talk about Children) or control group (treatment as usual). Participant randomisation will occur at the level of the treating practitioner and will be based on whether the randomised practitioner is trained in the intervention. Outcomes are compared at pre, post intervention and six-month follow-up. Recovery, parenting and family functioning, and quality of life questionnaires will be used to measure parent wellbeing and the economic benefits of the intervention.

**Discussion:**

This is the first randomised controlled trial to investigate the efficacy of a parenting intervention on recovery outcomes and the first to provide an economic evaluation of an intervention for parents with a mental illness. An implementation model is required to embed the intervention in different sectors.

**Trial registration:**

The trial was retrospectively registered: ACTRN12616000460404 on the 8/4/2016.

## Background

A significant proportion of individuals with a mental illness are parents who are caring for dependent children. Nicholson [1] found that 38% of women with serious mental illness were mothers, while another study [2] estimated that 21 and 23% of all families have at least one parent who has (or had) a mental illness. Parenting is a valued social role and for those with a mental illness provides meaning, purpose and identity [1] all core components of a personal recovery approach. Thus, a recovery intervention that encapsulates a service user’s parenting role and responsibilities holds much promise.

While the medical model of recovery emphasises the remission of mental health symptoms, the personal recovery model has been defined as a ‘change in outlook that is related to leading a meaningful, purposeful life, with or without ongoing episodes of illness’ [3].^(p268)^ Personal recovery is a complex concept that encompasses multiple life domains such as community engagement and employment [4], however little attention has been paid in the literature to the role of parenting within personal recovery frameworks [5]. Nicholson [1] found that children give parents the strength and will to ‘keep going’ thereby promoting hope (a key element of recovery). ‘Being a parent’ and effectively assuming the parenting role, provides parents with meaning and purpose (another element of recovery [1]). Parenting may also contribute positively to individuals’ lives by providing opportunities for meaningful interactions and activities [5]. Thus, identifying and supporting an individual’s parenting role can provide hope, a sense of agency, self-determination and meaning, all aligned with a recovery approach.

While there are some, albeit limited, evidence based interventions designed for families where a parent with a mental illness, approaches rarely consider how recovery and parenting might be aligned. Instead, most appear to be formalised interventions that promote psycho-education and family communication and, on the whole, are predominately designed for mothers with affective disorders [6]. There is, however, emerging evidence as to the effectiveness of interventions for parents with a mental illness and/or their children; Siegenthaler, Munder and Egger [7] employed a systematic review and meta-analysis of the effectiveness of 13 interventions designed to prevent mental illness in the children of parents with a mental illness. Across the 13 trials including 1490 children of parents with mental illness, interventions decreased the risk of developing mental illness for such children by up to 40%, predominantly through parent or family mediated programs [7].

One of the studies reviewed by Siegenthaler was the Let’s Talk about Children (Let’s Talk) approach. Let’s Talk is a two to three session intervention designed for parents with the mental illness [8]. In the intervention, parents are empowered to develop their own strategies to promote child and family strengths and discuss ways to talk to their children about their mental illness. In this process, practitioners engage with their parent-client in a discussion around the children that focusses on their strengths and any concerns the parent may have about their child. While other family members might be involved in these sessions, the focus is typically on empowering the parent with a mental illness in his or her parenting role. This clinical stance seeks to empower parents, so they may acquire the confidence, understanding and skills to promote change in their family. The program has been previously trialled in over two thirds of Finland’s health regions [9], with one RCT study reporting an increase in parents’ understanding of the impact of mental illness and on reductions in children and parents’ guilt, shame and perceived prejudice [8, 9]. Notably, training practitioners in the intervention led to significant practice changes, with a 16% increase in onward referrals for children to other services following the intervention [8].

Given the focus of Let’s Talk on parent empowerment and family strengths, the intervention is well aligned to personal recovery, relevant to parents with various disorders and levels of disability and applicable to different workforce sectors. How Let’s Talk impacts on recovery has not been investigated. Additionally, as highlighted by Bee and colleagues [10] no economic evaluations, cost or resource-use studies have been conducted in this area, an often critical consideration for governments when allocating funding and resources.

This study will examine the impact of an Australian-first parent recovery approach that incorporates Let’s Talk across three service sectors. The three service sectors include adult mental health, community mental health and family services in Victoria, Australia. Adult mental health services are a specialist clinical public service for people with a severe mental illness, including significant levels of disturbance and psycho-social disability; the service includes acute inpatient and continuing care facilities. The community mental health sector, sometimes known as psychiatric rehabilitation, includes non-government mental health community support services, designed for those with a chronic mental illness. Community practitioners work collaboratively with their clients on individual support plans, that are recovery focused. The family services sector offers support to vulnerable families with children at-risk, where risk factors include parental mental illness, family conflict or breakdown and problems related to child development, school attendance and social or economic disadvantage. Clients across all three sectors present with a wide range of mental illnesses including psychotic disorders, bipolar disorder, as well as affective disorders. However, parents in the family service sector, compared to the other sectors, are generally considered to present with less severe mental health problems, but with a high comorbidity of family violence and alcohol and other drug issues. The Let’s Talk approach is considered suitable for all levels of mental illness severity ([name] 2013, personal communication) but requires stability of symptoms for parents to engage in the intervention. Those parents in an acute stage of symptom presentation are recommended not to engage in the intervention.

The research will establish an evidence base for a recovery model that effectively addresses parenting, as measured by adult recovery (e.g. quality of life, hope, social inclusion), parenting competence and self-efficacy, family functioning. It is hypothesized that:Significant improvements (*p* < 0.5) will be reported by parents on the eight psycho-social dimensions of recoverySignificant improvements (*p* < 0.5) will be reported on parenting sense of competence and parenting self-efficacySignificant improvements (*p* < 0.5) will be reported on family functioning.

The study will also examine the economic value of a larger roll out (longer term) of the parent recovery model for investment by Victorian and Australian governments.

## Methods

### Design

This two-arm parallel randomised controlled trial will compare outcomes at post-test and 6 month follow-up (Trial register number ACTRN12616000460404) for Let’s Talk and control participants from the adult mental health, community mental health and family services. The protocol is in accord with the CONSORT-EHEALTH checklist. The study commenced in 2013 and will be completed in 2017.

### Study population

Clients who are parents in treatment at adult mental health, community mental health and family services sectors in Victoria, Australia will be the participants in this study. Mental illness is defined according to DSM-5 [11]; as a clinically significant disturbance in an individual’s cognition, emotion regulation, or behaviour that reflects a dysfunction in the psychological, biological, or developmental processes underlying mental functioning. Client eligibility includes; a mental illness diagnosed by either a GP or mental health practitioner, be between the ages of 18 and 65, have at least 20% custody of at least one child under 18 years of age, be attending services for their mental health problems, able to comprehend English and deemed (by their treating practitioner) to have the mental health capacity to participate in the research and intervention.

### Recruitment

Participating organisations will be recruited through an expression of interest process and public forums. Practitioners will be nominated by the organisation if they show an interest in family sensitive practice and/or have parent-clients with mental health issues on their current caseload. Eligible parents will be invited by their treating practitioner to be involved in a research study about recovery and families. At this point they will not be given any information about the intervention. The practitioner will give their parent-client a brief introduction to the research including a consent form. No information will be given to participants about the specific intervention as a description of the intervention (which highlights the parenting role and the needs of children) may possibly influence participants, particularly those who may not have considered or discussed their parenting role in relation to their illness. Parents interested in participating in the research will then authorise the practitioner to forward the parent’s contact details to the researchers. The researchers will then contact the parent-client (e.g. by phone, email) with comprehensive information (including written) of the research (not the Let’s Talk intervention) and will obtain consent from those interested in continuing in the research study. At this point, potential participants will be told that the research is about recovery and mental illness (not about parenting and children). All consenting parents will be sent a questionnaire pack and a reply paid envelope and will be offered phone assistance to complete questionnaires.

Following parent completion of the first questionnaire pack, the practitioner will be randomised to either the (1) wait list control group or (2) to receive training and deliver the Let’s Talk intervention. Randomisation has been designed to occur at the practitioner level to address any potential effects of attending Let’s Talk training in the control condition. The researchers will be blind to the allocation of the practitioner, with an independent administrative officer (based at a different site to the research team) allocating practitioners to groups based on the computer generated random sequence (using SPSS). Within 1 month after being allocated, Let’s Talk practitioners will be provided with training in the intervention. The control practitioners will continue treatment as usual and will not be trained in the intervention until completion of the study. Practitioners trained in the intervention will then offer Let’s Talk to their clients. Those parent-clients who decline the intervention will continue with treatment as usual with their practitioner (and continue in the research study if they wish as a separate comparison group in the analysis). Both wait-list control and Let’s Talk trained clinicians may refer any number of eligible parent-clients to the study who indicate interest in the research.

The control group will continue to receive ‘treatment as usual’ from their non-trained (in Let’s Talk) practitioner and will be informed about (and offered) Let’s Talk as they complete the final follow up questionnaire (following the training of their treating practitioner). Treatment as usual refers to the standard treatment or model of care usually provided to clients of each of the services involved in the trial. For the purposes of the trial this will be identified as treatment as usual in adult mental health clinical services, non-government mental health community support services and family support services.

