### Data collection

Participants will complete measures prior to randomisation and 6 weeks post the completion of the Let’s Talk intervention (including an equivalent time frame for the control group) and 6 months after the post test. Participants will have the option to complete their questionnaires by hand (and post their questionnaire), verbally over the phone or in person with one of the members of the research team.

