## Limitations

It is noted that practitioners recruited to the study may have a strong interest in family focused practice and/or have previously worked with parents with mental illnesses. Thus trial outcomes may potentially be biased by a practitioner’s willingness to already engage in the concerns of parents with mental illness. However, the nature of the randomisation of practitioners to receive training should address this concern.

Parents’ diagnoses will be self-reported by the participating parent, and is not independently verified. Parents will be asked who provided them with a diagnosis. In addition, during the first data collection, researchers will be blind to the allocated grouping. As the study unfolds however, parent contact with the researchers may be required (e.g. reminders, assistance completing questionnaires). Consequently, blinding may be lost for some participants at post-test and follow up. The number and circumstance of participant unblinding will be recorded on an ongoing basis by the research manager as will any adverse outcomes or events from the research and/or Let’s Talk implementation. The control parents may also acquire some knowledge of the research aims, as the measures include parenting instruments. In addition, while control practitioners will not have received training in Let’s Talk, they will be aware of the aims of the research study and may inadvertently transmit this (verbally or through their behaviour) during treatment as usual to the parents in the control group.

Critically, the RCT design of the study occurs in an applied setting and involves three different sectors. Hence, the study design may be susceptible to fidelity and implementation problems. Given that a significant time lag exists in the translation of research to practice in mental health [19], the study will require a sound implementation framework across the various workforce sectors.

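### The protocol sets no cut-off on referral at the practitioner's allocation, so parents may be selected and measured at baseline by a practitioner who already knows the arm, contrary to its own statement that baseline precedes randomisation.

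*Protocol article*

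**What the plan says.** All references are to the protocol article.

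- **Unit.** Recruitment states: "Randomisation has been designed to occur at the practitioner level".
- **Order of events.** Recruitment states: "Following parent completion of the first questionnaire pack, the practitioner will be randomised". It does not say whether this waits for one parent's pack or for the packs of all that practitioner's parents. Training comes next: "Within 1 month after being allocated, Let’s Talk practitioners will be provided with training in the intervention".
- **Who may refer.** The same section then names wait-list control practitioners and Let's Talk practitioners together and says that "trained clinicians may refer any number of eligible parent-clients to the study who indicate interest in the research". It gives neither a cap nor a closing date.
- **Baseline.** Data collection states: "Participants will complete measures prior to randomisation".
- **Gatekeeper.** Under Recruitment, the treating practitioner makes the invitation. Under Study population, a parent must be "deemed (by their treating practitioner) to have the mental health capacity to participate in the research and intervention".
- **Blinding.** Recruitment keeps the researchers blind to allocation and uses an independent officer at another site to allocate. Practitioners are not blind, since they either are or are not trained. Limitations adds that control practitioners will not be trained but that "they will be aware of the aims of the research study".

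**The concern.** When practitioners are randomised, the parents in the two arms are comparable by design only if they were identified before allocation, or by someone who did not know it. Here the person who invites parents and judges their capacity knows the arm once allocation has been made. If referral continues past that point, a practitioner about to deliver the intervention may choose different parents from one who is not. Randomising practitioners balances practitioners. It does not balance parents chosen afterwards.

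Limitations relies on the randomisation of practitioners to deal with their prior interest in family-focused work, but does not consider the choice of parents after allocation.

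A second, smaller matter is concealment. Recruitment withholds the parenting focus from parents before consent. That is harder to maintain when the inviting practitioner has already been trained in the intervention, so the concealment may be weaker for those parents.

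**Working it through.** **1. Does the text permit referral after allocation?** Setting the statements side by side:

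- Recruitment gives the order: first pack, allocation of the practitioner, training within a month of allocation.
- The referral sentence identifies the referrers by arm and training status. A practitioner acquires those labels only after allocation and training. No cut-off follows.
- The Methods paragraph of the Abstract bases a parent's group on whether the randomised practitioner is trained, which fits a parent entering an arm that is already fixed.
- Limitations says that researchers are blind to grouping during the first data collection. Had every baseline preceded allocation, there would be no grouping to be blind to.
- Data collection says the opposite: baseline comes before randomisation. That cannot hold for a parent referred by a practitioner who is already trained.

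So the text permits late enrolment without asserting that it happens, and the two sections disagree.

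**2. Do the stated safeguards reach the point of selection?** Researcher blinding and independent allocation protect other steps. Withholding intervention details governs what parents are told, not whom the practitioner approaches. At least one parent per practitioner appears to be enrolled before allocation, so any exposure is partial.

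**3. Size, as illustration only.** The plan's own total reproduces: 32 × 3 sectors × 2 arms = 192, so 96 per arm. The document gives neither the share of late referrals nor any difference in selection. Assume that a share q of the intervention arm is referred late and that those parents differ at baseline by d SD. Then

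- baseline imbalance = q × d;
- standard error = √(2/96) = 0.144 SD, ignoring clustering;
- chance of a significant baseline difference (two-sided 5%) = 1 − Φ(1.96 − qd/0.144) + Φ(−1.96 − qd/0.144).

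| q (assumed) | d (assumed) | imbalance | chance of p < 0.05 at baseline |
|---|---|---|---|
| 0.25 | 0.2 | 0.05 SD | 6.4% |
| 0.50 | 0.3 | 0.15 SD | 18% |
| 0.75 | 0.5 | 0.375 SD | 74% |

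Without differential selection the chance is 5%.

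**4. What reaches the treatment effect?** Quantitative data analysis plans analyses of variance with time within subjects and group between subjects. If late parents differ by the same d at every visit, the between-arm difference in change is q × (d − d) = 0, so the group-by-time interaction is unaffected. If they differ by c SD in how they change over time, the interaction is shifted by q × c. The document offers no basis for a value or a sign of c.

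**The case against.** The strongest reply is that enrolment after allocation is inferred. The referral sentence may mean only that there is no limit on parents per practitioner, with the arm names used as labels, and two statements about timing put the first questionnaire before randomisation. This reading is possible, so the point must be put as something the text permits. It does not remove the conflict. Recruitment sets no cut-off, and its reference to the first pack does not say whether all of a practitioner's parents must have completed it.

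That a condensed article may leave a referral cut-off to the full protocol is fair as regards missing detail. It does not cover two sections of the article that disagree.

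Three stronger readings are tempting but not supported:

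- **That the concealment fails for parents of trained practitioners.** Recruitment withholds the intervention from all participants without exception, and researchers, not practitioners, obtain consent. Leakage is possible but not shown. Limitations also acknowledges that control practitioners may pass on the study's aims, so the risk is not confined to one arm.
- **That trained practitioners will select favourable parents, or that late baselines already carry part of the effect.** The capacity criterion is the same in both arms, and control parents are offered Let's Talk at the end. Nothing suggests that the intervention is delivered before a parent's baseline.
- **That 0.05 to 0.15 SD is a spurious treatment difference.** Those figures come from assumed inputs and describe an imbalance at baseline. A constant imbalance cancels in the interaction.

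**Conclusion.** The point stands as an internal conflict with a possible bias behind it. As written, Recruitment lets parents be invited, judged to have capacity and measured at baseline after allocation by a practitioner who knows the arm, while Data collection says that baseline precedes randomisation. Differential selection by arm is therefore possible.

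Its size and direction cannot be computed from the document. The imbalances shown above depend wholly on assumed values of q and d. For the group-by-time comparison, only selection related to change over time would matter, and this cannot be estimated here. A reader should not infer that late enrolment has occurred, or that the trial's result is biased by any stated amount.

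**What to change.** Reconcile Recruitment with Data collection by stating that all of a practitioner's participating parents are identified, consent and return the baseline pack before that practitioner is allocated. Their number need not be capped.

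The study commenced in 2013, so this may come too late for some practitioners. For those already allocated:

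- record each parent's consent and baseline dates against the practitioner's allocation date;
- report numbers and baseline scores by arm, separately for parents referred before and after allocation;
- keep all parents in the intention-to-treat analysis;
- add a prespecified sensitivity analysis limited to parents enrolled before allocation.

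Restricting the primary analysis to early referrals is not recommended. If 25% to 50% were late (an assumption), it would leave 192 × 0.75 = 144 down to 192 × 0.50 = 96 parents, or 24 down to 16 per sector per group against the planned 32. It would also sit poorly with the stated intention-to-treat approach.

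The cost is slightly longer recruitment before each allocation and a little more analysis work. The date check also requires both sets of dates to be available, which the article does not confirm.
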